#### B - Interviews with health professionals of the intervention group

The third component of the process evaluation comprises of semi-structured interviews with participants in the intervention arms of the trials. The face-to-face interviews (or, alternatively, telephone interviews) will be done with a purposive sample of health professionals. The exact phrasing of questions will differ across trials, but the following interview format will serve as a starting point for all interviews:

1. What made you participate in the project in the first place? What where your reasons and what were your expectations?

2. Did the implementation program help you to adhere to the recommendations?

a. If yes, what components did you find helpful and why?

b. If no, why not and what strategies would have been more helpful?

3. Were there any other factors or developments which made it difficult for you or helped you to adhere to the recommendations? You can think of changes in regional or national healthcare, developments in the practice organization and team or events in your life and work.

4. Having experienced the program, what would you recommend for the future? You may think of further development, wider implementation or perhaps research.

Interim analysis after 5 to 10 interviews will be done to adapt the interview format and purposeful sampling scheme as required.

#### C - Practice characteristics and other contextual factors

The success of an implementation program may be influenced by factors, which cannot, or at least cannot easily, be addressed, such as the structure of the health system, laws or the organizational structure of the targeted settings [16]. The TICD studies are focused on primary care. In four TICD studies a number of practice characteristics will be recorded in both study arms (Table 3). This is not feasible in the Norwegian study, where municipalities are the unit of randomization. In Norway, information regarding relevant characteristics of the municipalities and specialist health care that may modify the effectiveness of the interventions will be collected instead.

**Table 3 T3:** Practice characteristics determined in all Tailored Interventions for Chronic Diseases (TICD) studies (C)

		
1.	What is the yearly attending population (number of different patients that contact the practice in one year)?	
2.	What is the number of contacts your practice has per week?	
3.	How many physicians are working in your practice? (full-time equivalent)	
4.	How much non-physician staff is working in your practice? (full-time equivalent)?	
5.	How many inhabitants live in the city where your practice is located?	o <5,000
		o >5,000 <20,000
		o >20,000 <50,000
		o >50,000
6.	Do all physicians have access to medical guidelines in your practice?	o yes o no
7.	Is a recall system for follow-up of chronically ill patients used in your practice?	o yes o no
8.	Are the tasks in your practice clearly assigned to specific staff?	o yes o no
9.	Does your practice have regular team meetings?	o yes o no
10.	Did your practice set targets for quality improvement in the last 12 months?	o yes o no
11.	Has the principal target (regarding quality improvement) been met?	o yes o no

### Data analysis

We will use the following analytical approach to answer the research questions addressed by this process evaluation:

1. Research question 1 - To what extent did the practitioners or patients use the various components of the planned intervention programs? and

2. Research question 2 - What is the validity of the methods used to tailor the implementation program to determinants of practice?In order to answer these questions a descriptive analysis of qualitative and quantitative data will be done separately in each country. The descriptive analysis of questionnaires will result in tables with frequency distributions. The qualitative interviews will be transcribed verbatim in the original languages. An iterative thematic analysis will be done, involving two or more researchers in order to identify key themes relevant for implementation.

3. Research question 3 - Which factors are associated with implementation of evidence-based practice in chronic illness care, after use of a tailored implementation program?

To answer this research question a summary outcome measure will be constructed in each trial, expressing professional performance by aggregating items reflecting implementation of evidence-based recommendations. This outcome will be standardized and taken as dependent variable in a regression analysis approach. The independent variables in this model will be a limited number of questionnaire items (to reduce chance capitalization), selected according to hypothesis informed by relevant key themes of the interviews. A special focus will be given to the association between professional performance and the questionnaire items concerning the application and adaption of the implementation program by the target group.

4. Research question 4 - How consistent are the findings across the trials?

A meta-analysis of quantitative and a meta-ethnography of qualitative data from all five studies will be conducted.

A qualitative meta-ethnography will be conducted using the data from the interviews. For this purpose a description of subcategories with significant quotations from all studies will be provided in English. This material will be analyzed according to the principles of Noblit and Hare’s reciprocal translational analysis, which is recommended to be used when analyzing studies with similar topics [17,18]. The result of this analysis will be a set of key themes relevant in all studies. Interviews will be re-analyzed to explore how each single study contributes to the overall key themes. In a last step third order interpretation across the key themes will be considered if supported by a ‘line of argument’ across all studies.

A quantitative meta-analysis will be conducted, focused on the summary outcome measure in each trial, using the predictors that are identified as result from the analysis for question 3. While the items composing this aggregate outcome obviously differ among the trials, the assumption is that the resulting measures are reasonably comparable to allow pooling. Based on hypotheses derived from phase 1 and 2, individual data and/or clustered data from all trials will be included in a meta-regression analysis. This last step will efficiently make use of the total number of cases included across all studies and the shared instruments as described in this protocol.

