## Abstract

**Background:**

In the ‘Tailored Implementation for Chronic Diseases (TICD)’ project, five tailored implementation programs to improve healthcare delivery in different chronic conditions have been developed. These programs will be evaluated in distinct cluster-randomized controlled trials. This protocol describes the process evaluation across these trials, which aims to identify determinants of change in chronic illness care, to examine the validity of the tailoring methods that were applied, and to analyze the association of implementation activities and the effectiveness of the program.

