## Background

‘Tailored interventions’ are commonly defined as interventions that are designed to address previously identified determinants of practice (also called ‘barriers to and enablers of change’) [1]. A range of different methods has been used for tailoring, but there is little insight into how tailoring is best conducted in order to optimize the effectiveness of interventions [2]. The overall aim of the ‘Tailored Implementation for Chronic Disease (TICD)’ project is to provide insight into methods for tailoring implementation programs to determinants of implementation of evidence-based healthcare for patients with chronic illness [3]. Research teams from five European countries participate in the TICD project, each focusing on a specific clinical condition: chronic obstructive pulmonary disease (COPD) in Poland, obesity in the United Kingdom, cardiovascular diseases in The Netherlands, depression in the elderly in Norway, and multimorbidity in Germany.

Addressing the identified determinants of practice in chronic illness care requires complex interventions, meaning interventions that have multiple components which interact with each other. In the TICD project, five tailored implementation interventions were developed, each of which will be evaluated in a cluster-randomized trial [4-8].

A frequent criticism of evaluations of complex interventions is their lack of detail in both description and analysis on what components of the intervention and which contextual factors contributed to the (lack of) effectiveness [9]. We planned process evaluations in the TICD trials aiming to address this by exploring which factors are associated with change [10,11]. This knowledge is essential for understanding the potential causal mechanisms underlying the effectiveness of interventions as well as for ensuring generalizability of intervention effectiveness across populations and settings [12]. At the same time, this will provide insight into the validity of tailoring methods that were applied in earlier phases of the TICD project.

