A factor of specific interest is the degree to which the offered interventions were applied as planned by the participants (depending on the context this has been labeled ‘fidelity’ or ‘integrity’ of the intervention [13]). This knowledge is important to draw valid conclusions about intervention effectiveness and the underlying change mechanisms. Potentially useful interventions may appear ineffective due to low or mistaken application as compared to the original plan [13]. On the other hand, low fidelity or integrity may reflect the adaptation of interventions in the delivery phase to optimize their effectiveness.

Here, we aim to describe the planned process evaluations that are intended to answer the following questions:

1. To what extent did the practitioners or patients use the various components of the planned intervention programs?

2. What is the validity of the methods used to tailor the implementation program to determinants of practice?

3. Which factors are associated with effective implementation of evidence-based practice in chronic illness care, after use of a tailored implementation program?

4. How consistent are the findings regarding the previous questions across the five trials?

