#### A1 - Survey on perceived change of determinants of practice

We will perform written surveys in participating health professionals at the primary follow-up measurement in the trials (except in the Norwegian trial, where this survey is considered to be not feasible). As the content of the studies differs, we have developed a frame of the questionnaire that needs to be adapted to the relevant content (Table 1). The questionnaire lists the determinants of practice, which were identified and prioritized in an earlier phase of the TICD project (regardless of whether they are addressed by the implementation program), with the question to assess whether the program successfully targeted them. A free text field is used to identify other determinants that are lacking from this list and are perceived to have major impact.

**Table 1 T1:** Scheme of a questionnaire to examine the validity of the methods used for tailoring (A1)

**Standardized list of determinants (result of phase 2). Please list all determinants, no matter if they are intended to be addressed by the implementation program or not**	**Was this determinant in your opinion clearly addressed by the implementation program?**		
	**Yes**	**Partly**	**No**
Determinant 1	□	□	□
Determinant 2	□	□	□
…			
Free text field: Can you think of other factors, not yet listed above?			

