## Conclusions

Process evaluation is essential to understand the effects and to explore potential causal mechanisms of complex interventions. The planned process evaluation in the TICD project needs to find a balance between standardization of methods across trials and adaptation of measures to the specific characteristics of each trial. Despite obvious limitations, such as heterogeneity and suboptimal statistical power, we believe that the planned study will contribute to our knowledge on determinants of change in chronic illness care and methods for tailoring implementation programs to barriers and facilitators of change.

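### The evaluation aims at determinants of change, but the research question 3 regression models a level of performance and names no prior-performance term, so as written it cannot tell improvement from prior standing

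*Protocol article*

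**What the plan says.** **Aim.** The abstract's Background says that the process evaluation "aims to identify determinants of change in chronic illness care". The main Background section speaks of "exploring which factors are associated with change", and the Conclusions expect the study to "contribute to our knowledge on determinants of change in chronic illness care".

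**Research question 3.** The Background words it as "Which factors are associated with effective implementation of evidence-based practice in chronic illness care, after use of a tailored implementation program". Data analysis repeats the question without the word for effective.

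**Model.** Under Data analysis, each trial builds an aggregate score of how far the recommendations are carried out. Then: "This outcome will be standardized and taken as dependent variable in a regression analysis approach". The other side of the equation is also given: "The independent variables in this model will be a limited number of questionnaire items (to reduce chance capitalization"). Interview themes guide the choice of items, with special attention to those on use and adaptation of the programme.

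**Timing and population.** Section A1 states: "We will perform written surveys in participating health professionals at the primary follow-up measurement in the trials", with Norway excepted. The section on setting and target groups defines the study population as the intervention-group professionals. The timing of the performance score is not stated.

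**Carry-forward.** The quantitative meta-analysis in Data analysis uses the predictors that question 3 identifies.

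**The concern.** A level and a change are different quantities. A practice that already followed the recommendations before the programme may report full use and coverage and call the components helpful, and also score high at follow-up, without having improved. A regression of the later score on those survey answers would then show an association that reflects where the practice started.

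Nothing else in the described model guards against this. There is no randomized contrast behind an association among intervention-group professionals, and the survey answers are collected at follow-up. The use items are exactly those to which question 3 gives special attention. If the model selects an item for this reason, the item goes on to the pooled analysis, where a larger sample makes the same bias easier to declare significant. The Conclusions acknowledge heterogeneity and limited power, but not this limitation.

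**Working it through.** **Step 1: aim against model.** The article has no sample size, significance level, effect size or correlation, so it has no figure of its own to reproduce. The comparison is textual.

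| Element | What the article gives | Where |
|---|---|---|
| Aim | determinants of, or factors associated with, change | Abstract, Background, Conclusions |
| Dependent variable | standardized performance score; no change score | Data analysis |
| Independent variables | a small set of survey items; no prior performance named | Data analysis |
| Time of survey | primary follow-up | A1 |
| Time of performance score | not stated; the question's reference to the period after programme use implies follow-up | Background, Data analysis |
| Study population | intervention-group professionals | Setting/target groups |

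Standardizing puts the scores on one scale but does not turn a level into a change.

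**Step 2: what the omission does.** Let b be baseline performance, x the survey item and y follow-up performance, each with mean 0 and variance 1. Let r = corr(x, b) and ρ = corr(b, y). Suppose that x has no effect on y given b:

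- x = r·b + e and y = ρ·b + u, with e and u independent of b and of each other.
- Slope of y on x alone: cov(x, y) = r·ρ.
- Slope of y on x with b in the model: (rρ − rρ)/(1 − r²) = 0.

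For assumed r = 0.4 and ρ = 0.6, the unadjusted slope is 0.4 × 0.6 = 0.24. For r = 0 it is 0. For negative r (weaker practices using the programme more) it is negative, and could mask a real association.

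**Step 3: illustration of error rates.** All inputs are assumed: independent observations, two-sided test at 0.05, 4,000 simulated data sets per setting, no effect of the item given baseline.

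| ρ | r | rρ | Rejection without baseline, n = 60 | Rejection without baseline, n = 200 |
|---|---|---|---|---|
| 0.3 | 0.2 | 0.06 | 8% | 13% |
| 0.5 | 0.4 | 0.20 | 34% | 82% |
| 0.7 | 0.4 | 0.28 | 60% | 98% |
| 0.3 to 0.7 | 0 | 0 | about 5% | about 5% |

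With baseline as a covariate, rejection was 4.2% to 5.7% over all settings run (n = 30 to 200, ρ = 0.3 to 0.7, r = 0 to 0.4). For r = 0.4 and ρ = 0.6, unadjusted rejection was about 18% at n = 20, 32% at n = 40, 58% at n = 80 and 87% at n = 160.

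**Step 4: limit of the adjustment.** Step 3 treats the baseline score as error-free. If the recorded score has reliability k, its correlations with x and y are r√k and ρ√k, and the adjusted slope is rρ(1 − k)/(1 − r²k). This is 0 at k = 1 and returns to rρ at k = 0. A noisy baseline score therefore reduces the bias without removing it.

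**The case against.** The strongest reply is that this is a condensed article. It leaves the construction of the score to each trial, and neither the trial protocols nor an analysis plan is shown. The article does not mention baseline data, but does not rule them out either. That much stands: the follow-up timing is an inference, and a fuller plan might contain the covariate. But the article is not merely silent. It describes both sides of the model, and that description does not match the aim.

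Second, the main Background treats determinants of practice as another name for barriers to and enablers of change, so the aim may be the field's term for what helps or hinders uptake. Question 3 itself asks only about association after the programme, which this regression can answer. That is a fair reading of the question. It does not cover the Background's separate statement about factors associated with change. If only level is meant, the conclusions should say so.

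Third, the practice characteristics in Table 3, such as recall systems and quality targets, may partly stand in for earlier quality, and the interviews probe other influences on adherence. These help somewhat, but none is a prior performance score.

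Fourth, the direction and size of any bias are unknown. This stands in full.

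A reader might infer that the trials will report mere markers of prior performance as drivers of change, or that the error rates above are this plan's error rates. The article supports neither. It words question 3 as association, bias arises only for items correlated with baseline, and every correlation and sample size used here is assumed.

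**Conclusion.** The point holds in a limited form. The research question 3 model, as the article describes it, cannot distinguish factors associated with improvement from factors that track prior performance, so it does not deliver an aim stated in terms of change. The weakness passes to the pooled analysis through the selected predictors.

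Its size cannot be derived from the article. The spurious standardized slope is the product rρ: none if an item is unrelated to baseline, 0.06 to 0.28 over the non-zero assumed correlations in the table. The conclusion rests on reading the performance score as a post-programme level and on there being no unstated baseline term. It should be corrected while the trial is still in planning, as the article reports. It does not undermine the descriptive or qualitative parts of the evaluation.

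**What to change.** 1. State when the summary performance score is measured in each trial.
2. In trials that collect the component items at baseline, build the same score from the baseline data and enter it as a covariate in the question 3 regression and in the pooled model.
3. In trials without those items, limit the conclusion to associations with performance level after the programme, and keep these results distinguishable from the adjusted ones when pooling.
4. Use the same terms in the aim, the question and the conclusions, so that change is claimed only where baseline is in the model.

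The cost is one degree of freedom per model and some extra scoring. The article does not list baseline variables, so whether each trial holds the items has to be checked first. Residual confounding can remain if the baseline score is noisy, and the report should say so. Where no baseline score exists, the cost is a narrower claim.

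### The stated qualitative result for research question 4 holds only themes shared by all studies, so the cross-trial answer on consistency has no place for divergent or conflicting themes

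*Protocol article*

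**What the plan says.** The Background of the protocol article lists four research questions. The fourth reads "How consistent are the findings regarding the previous questions across the five trials". The Data analysis section assigns it a two-part method: "A meta-analysis of quantitative and a meta-ethnography of qualitative data from all five studies will be conducted".

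**Qualitative part.** Subcategories with illustrative quotations from every study are put into English and analysed by reciprocal translation, "which is recommended to be used when analyzing studies with similar topics". The product is then stated: "The result of this analysis will be a set of key themes relevant in all studies". Two steps follow:
- The first is a return to the transcripts: "Interviews will be re-analyzed to explore how each single study contributes to the overall key themes".
- The second, a third-order interpretation, is optional. It depends on whether one line of argument runs through every study.

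**Quantitative part.** The meta-analysis concerns the summary performance outcome of each trial and uses the predictors that emerge from question 3. The article concedes the differences in content ("While the items composing this aggregate outcome obviously differ among the trials") and continues that "the assumption is that the resulting measures are reasonably comparable to allow pooling". A meta-regression on individual or clustered data is also planned, and its stated benefit is efficient use of all cases.

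**The concern.** A question about consistency needs an output that can show inconsistency. In a qualitative synthesis, that means themes that appear in some trials and not in others, or that point in opposite directions. The stated product contains only what is relevant everywhere.

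Disagreement is plausible here. The Background describes five countries with five different conditions, and section C notes that Norway randomises municipalities, so its setting differs from the practice-based trials. If an implementation factor matters in two trials and is absent or reversed in the other three, that is a direct answer to question 4. Followed as written, the cross-trial report could list common themes and pooled associations and leave such a pattern to be found by comparing separate country reports.

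**Working it through.** The article gives no sample size, threshold or effect size for question 4, so there is no figure to reproduce. The check sets the question beside each stated output.

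| Stated step (Data analysis) | What it can show | What it has no stated place for |
|---|---|---|
| Reciprocal translation leading to shared key themes | Themes relevant in all studies | Themes present in only some trials |
| Re-analysis of interviews by study | Strong or weak contribution of a study to a retained theme | Themes not retained |
| Third-order interpretation | An interpretation supported across all studies | An interpretation that holds in some trials only |
| Meta-analysis and meta-regression | Associations for the question 3 predictors, using all available cases | Qualitative themes |
| Country-level analyses for questions 1 and 2 | Each country's own frequencies and themes | Any comparison between countries |

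1. The first three rows are the whole qualitative path to question 4. The first and third carry an all-study condition. The second works on the output of the first.
2. Question 4 refers to all the preceding questions. As the article describes it, the quantitative synthesis takes up only the question 3 predictors. For questions 1 and 2, the only cross-trial synthesis it describes in any detail is therefore the meta-ethnography, and that is where the restriction sits.
3. The country-level analyses do hold divergent themes, but the article assigns them to questions 1 and 2. It does not name them as the means of answering question 4.
4. The quantitative part is narrower than the phrase about all five studies suggests. The question 3 predictors are questionnaire items. The Abstract and section A1 say that Norway does not run the survey, so questionnaire predictors come from at most 5 − 1 = 4 trials. The interviews can cover all five.

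**The case against.** The strongest reply is that the sentence describes an output and is not an exclusion rule. Nothing in the article says that a theme found in two trials is thrown away. A theme can be relevant everywhere and still work in opposite directions, and the re-analysis by study could bring that out. This stands in part: contrasts within a shared theme could be reported. It does not help a theme that never became a shared one.

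A reader might go further and infer that the plan presupposes agreement, or is designed to find it. The documents do not support that:
- Reciprocal translation is not the only device. The line-of-argument step is conditional, so the plan allows for support across studies to be lacking.
- The country analyses are kept separate, so differences stay in the record.
- A meta-regression can model differences between trials, even though the article presents it as a gain in cases.
- The comparability assumption is stated openly, the outcome is standardised, and the Conclusions name heterogeneity as a limitation.

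Nor is the lack of a named heterogeneity statistic or random-effects model a fault. A journal article may leave that to a fuller plan.

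One might also want the between-trial variance to become the primary answer to question 4. With four trials that is hard to defend. Even if the four trial-specific associations were normally distributed and known without sampling error, a variance on 4 − 1 = 3 degrees of freedom has a 95% interval whose upper limit is 9.35 / 0.216 ≈ 43 times its lower limit.

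**Conclusion.** The point holds for the qualitative synthesis: its stated output is narrower than the question it is meant to answer. Themes confined to some trials, or conflicting between them, have no stated place in the cross-trial result. This is a fault in an output that the article fixes, and a later plan that follows the sentence would inherit it.

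The consequence is limited. No data are lost, the country-level findings are unaffected, and only the reported answer to question 4 is at risk. The conclusion rests on reading the output sentence as it stands and on the re-analysis being confined to the retained themes, as the article says. How many themes would be affected cannot be estimated from the document.

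On the quantitative side, the conclusion is only that trial-specific associations should be visible beside the pooled one and that the number of contributing trials should be stated correctly.

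**What to change.** In the Data analysis section, replace the sentence that defines the qualitative result with:

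> The result is a theme-by-trial matrix showing each key theme as present, absent or contradicted in each of the five trials; shared themes are synthesised by reciprocal translation, and divergent or conflicting themes are reported alongside them.

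For the quantitative part, add that question 4 will be answered by showing the trial-specific predictor associations next to the pooled estimate, and that questionnaire predictors are available from at most four trials because Norway has no survey. A between-trial variance may be reported but should not be made the primary result.

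The cost is some extra synthesis and reporting from the same transcripts and models, with no new data collection. The article gives the project's status as still in planning, so the wording can be changed before the analysis begins.
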